### Cost-Effectiveness Analysis

Cost-utility analysis (CUA) will be used to explore whether the intervention provides health benefits at the individual level. CUA compares the incremental costs and benefits, expressed in quality-adjusted life years (QALYs) gained, of alternative programs. Health utilities will be derived from the EORTC QLU-C10D, a subset of 10 questions from the EORTC QLQ-C30 [110]. Costs will be obtained from a questionnaire that will be completed by the waitlist control and exercise groups prior to commencement of the intervention and during the 3-month supervised and 6-month unsupervised phases to determine individual costs associated with the intervention and other health resource utilization. Costs will be measured from a societal perspective and will include intervention costs, healthcare costs, costs of informal care, sports costs, unpaid productivity costs, and absenteeism costs. Healthcare costs include the costs of primary healthcare (i.e., general practice, physical therapist), secondary healthcare (i.e., outpatient care, hospitalization), and prescribed, as well as over-the-counter medication. The value of the resources consumed will be determined using unit prices from standard costing resources (e.g., Medicare Benefits Schedule, award wage schedules).

Resource utilization during the 3-month supervised and 6-month unsupervised phases will be recorded. This includes labor (e.g., to deliver the intervention and group classes) and non-labor (e.g., gymnasium use), as well as the cost of usual care provided by the hospital. Resource use will be costed at market rates (e.g., industrial award rates for labor costs) for use in cost-effectiveness analyses. The resource use associated with the exercise intervention delivery will include labor time, i.e., AEP hours planning the exercise sessions (e.g., phoning/meeting people to book their session, pre-exercise safety screening), delivering the exercise sessions, and documentation time for clinical notetaking. Time spent for research assessments will not be included. Resource use will also include non-labor costs associated with delivering the intervention from the perspective of the health service, e.g., cost of hiring gym space.

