## Abstract

People with multiple myeloma (MM) are second only to people with lung cancer for the poorest reported health-related quality of life (HRQoL) of all cancer types. Whether exercise can improve HRQoL in MM, where bone pain and lesions are common, requires investigation. This trial aims to evaluate the efficacy of an exercise intervention compared with control on HRQoL in people with MM. Following baseline testing, people with MM (*n* = 60) will be randomized to an exercise (EX) or waitlist control (WT) group. EX will complete 12-weeks of supervised (24 sessions) and unsupervised (12 sessions) individualized, modular multimodal exercise training. From weeks 12–52, EX continue unsupervised training thrice weekly, with one optional supervised group-based session weekly from weeks 12–24. The WT will be asked to maintain their current activity levels for the first 12-weeks, before completing the same protocol as EX for the following 52 weeks. Primary (patient-reported HRQoL) and secondary (bone health and pain, fatigue, cardiorespiratory fitness, muscle strength, body composition, disease response, and blood biomarkers) outcomes will be assessed at baseline, 12-, 24- and 52-weeks. Adverse events, attendance, and adherence will be recorded and cost-effectiveness analysis performed. The findings will inform whether exercise should be included as part of standard myeloma care to improve the health of this unique population.

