#### Stepped Down Supervision Approach

The modular multi-modal exercise program should be undertaken three times per week. For the first twelve weeks, two exercise sessions per week will be supervised by an AEP and once at home. For home-based sessions, elastic resistance bands will be provided, with advice for the purchase of dumbbells of appropriate weight. High intensity training will be replaced by a moderate intensity walk three times per week if a bike or treadmill is unavailable. Exercise supervision in the following three months will be stepped down to home-based sessions, with an optional weekly group class (2 to 6 participants) supervised by the study AEP. In addition, the AEP will telephone participants every two weeks to check on their adherence, any adverse events, prescribe progressions/regressions as appropriate, and answer any questions. Motivational interviewing will be used if any barriers are expressed. Following the first six months, all participants will be encouraged to maintain three exercise sessions per week for a further six months without group sessions. At the completion of their study involvement, participants will receive education regarding the Australian Government Department of Health Chronic Disease Management Plan, with no direct referrals to exercise physiologists or group classes.

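### Costs are collected over 3 + 6 = 9 months of a 12-month programme, and it is unclear whether the waitlist arm's usual-care period is costed

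*Protocol article*

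**What the plan says.** Under Cost-Effectiveness Analysis, the protocol article states: "Costs will be obtained from a questionnaire that will be completed by the waitlist control and exercise groups prior to commencement of the intervention". The full timing is "prior to commencement of the intervention and during the 3-month supervised and 6-month unsupervised phases". The next paragraph repeats the phases: "Resource utilization during the 3-month supervised and 6-month unsupervised phases will be recorded". Of that resource use it says: "This includes labor (e.g., to deliver the intervention and group classes". It also counts hospital usual care: "as well as the cost of usual care provided by the hospital". Utilities come from the QLU-C10D, which is scored from QLQ-C30 items.

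The programme is described elsewhere. The Abstract says: "From weeks 12–52, EX continue unsupervised training thrice weekly", and places the optional group session in weeks 12-24 only. The section Stepped Down Supervision Approach says of months 3-6: "Exercise supervision in the following three months will be stepped down to home-based sessions, with an optional weekly group class". It adds two-weekly telephone calls in that period, then a further six months with no group sessions. The Abstract and Table 1 place the QLQ-C30 at baseline, 3, 6 and 12 months. The waitlist arm has 12 weeks of usual care and then follows the same 52-week programme. A footnote to Table 1 says its baseline battery is repeated at the end of the wait.

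**The concern.** A cost-utility ratio needs costs and QALYs for the same people over the same period. Here the cost phases are shorter than both the programme and the utility follow-up, and the six-month label does not fit the phase structure given elsewhere. Costs that were never collected cannot be recovered later by an analysis plan, so this has to be settled in the data collection.

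The waitlist arm raises a second question. Weeks 0-12 are the only period in which a randomized group is on usual care alongside the exercise group. All cost windows after the first form are defined by exercise phases, and for the waitlist arm its own exercise phases begin only after the wait.

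The Discussion says the economic results will inform whether the programme could enter standard care, so incomplete costs would matter for that use.

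**Working it through.** **Inputs** (12, 24 and 52 weeks are treated as 3, 6 and 12 months, as the article does)

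- Cost and resource-use phases (Cost-Effectiveness Analysis): 3 months supervised and 6 months unsupervised.
- Programme (Abstract; Stepped Down Supervision Approach): 12 weeks supervised, 12 weeks stepped down, then six months (28 weeks) unsupported.
- QLQ-C30 (Abstract; Table 1): 0, 3, 6 and 12 months.

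**Durations**

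- Cost phases: 3 + 6 = 9 months.
- Programme: 12 + 12 + 28 = 52 weeks = 12 months.
- Part after full supervision: 52 − 12 = 40 weeks; 40/52 × 12 = 9.2 months, not 6.
- Coverage by the stated phases: 9/12 = 75%; gap 12 − 9 = 3 months (25%).
- If the unsupervised phase ran for 9 months, 3 + 9 = 12 would match both the programme and the QLQ-C30 schedule.

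**Possible readings of the six-month unsupervised phase**

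| Reading | Months costed | Months not costed | Evidence in the article |
|---|---|---|---|
| Final unsupported phase | 0-3 and 6-12 | 3-6 (3 months) | Fits the last six months under Stepped Down Supervision Approach, but omits the only months with the group classes that are to be costed |
| Six months straight after supervision | 0-9 | 9-12 (3 months) | Includes the group classes, but no utility is measured at month 9 |
| Label for the period up to month 6 | 0-6 | 6-12 (6 months) | Fits the Qualitative Analysis section, which speaks of a three-month unsupervised intervention, with interviews at month 6 in Table 1 |

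None covers 12 months.

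**What a mismatch could do (illustration only)**

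Assume a utility gain *d* over an unexposed comparator, zero at baseline, reached by month 3 and held to month 6. QALYs are the area under the curve by the trapezoid rule.

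- Gain sustained to month 12:
  - 0-12 months: 0.25 × d/2 + 0.25d + 0.50d = 0.875d.
  - 0-9 months: 0.125d + 0.25d + 0.25d = 0.625d.
  - Ratio: 0.875/0.625 = 1.40.
- Gain back to zero at month 12:
  - 0-12 months: 0.125d + 0.25d + 0.50 × d/2 = 0.625d.
  - 0-9 months, with 0.5d interpolated at month 9: 0.125d + 0.25d + 0.25 × 0.75d = 0.5625d.
  - Ratio: 0.625/0.5625 = 1.11.

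If 12-month QALYs were set against costs for months 0-9, the QALY gain would be 11% to 40% larger than the one that matches the costs. Over weeks 0-12 alone the gain is 0.125d. That is also the only stretch with an unexposed randomized comparator.

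**Waitlist arm**

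Its follow-up is 12 + 52 = 64 weeks from baseline. It fills in a form before the intervention, but the article does not say whether this is at enrolment or at the end of the wait, or what recall period the form uses. A form at enrolment would not cover weeks 0-12; a form at the end of the wait with three-month recall would.

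**The case against.** The strongest defence is that the phase names are loose labels rather than dated windows, and that the article's content shows what is meant. Because group-class labour is to be costed and classes run only in weeks 12-24, months 3-6 are presumably included. If the gap is months 9-12, no classes or calls are described then, so delivery cost is barely touched and only health-care and societal costs would be missing. This stands as an argument against the first reading, and for that reason no figure is put here on lost delivery cost. It does not close the gap, because the other two readings also stop short of 12 months or skip part of it.

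A reader might infer that the wait is excluded and that the 12-week incremental cost is out of reach. The article does not support that. The waitlist arm is named as completing the form before the intervention. The sections on the primary outcome and on statistical considerations use the supervised phase as the between-group period, which would make the wait a cost window. Hospital usual care is counted too. The wait is therefore unclear, not excluded.

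A reader might also infer that the planned ratio does combine different horizons. No QALY horizon is stated, and a common window could still be chosen, so this is a risk and not a stated plan.

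Finally, questionnaire dates and recall periods are often left to a full protocol or health-economic plan, and their absence from an article is no fault. The point here is the stated phase lengths, given twice, which do not fit the programme described in the same article.

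**Conclusion.** The point holds as an inconsistency in the article's own figures. The cost phases add up to 9 months, while the programme and the utility measurements run to 12. Followed as written, the text leaves at least 3 of 12 months uncosted, or 6 if the label means up to month 6. Which months are lost depends on the reading, and the article does not settle it. Whether the waitlist arm's costs in weeks 0-12 are captured is not assured.

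The consequence is conditional: a 12-month cost-utility comparison would risk pairing full QALYs with incomplete costs. The 11% to 40% illustration rests on the assumed utility paths and on costs ending at month 9. The matter is worth correcting because uncollected costs cannot be restored.

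**What to change.** 1. Reconcile the Cost-Effectiveness Analysis section with the Abstract and Stepped Down Supervision Approach by naming the phases once, with months: supervised (0-3), stepped down (3-6) and unsupported (6-12).
2. Give the cost questionnaire at the existing QLQ-C30 visits, with recall back to the previous visit. For the exercise arm this means baseline, 3, 6 and 12 months. For the waitlist arm it means baseline, the end-of-wait visit, and then the same points of its own programme. Show it in Table 1.
3. Use the same horizon for costs and QALYs, with weeks 0-12 as the randomized comparison. Present later periods separately, since the waitlist arm is then exercising too.

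The cost is a wording change and one or two extra questionnaires per participant at visits that already take place, with slightly more participant burden.

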## 6. Ethics and Dissemination

This study has institutional ethical approval through the Human Research Ethics Committees of Greenslopes Private Hospital, Metro South Hospital and Health Service, The University of Queensland, and QIMR Berghofer Medical Research Institute (#18/58 GREC; #HREC/2019/QMS/47400; #2018002644/18/58 UQ HREC; P#2352). Any future amendments to the protocol and/or associated documents will be submitted for approval to the aforementioned Human Research Ethics Committees. Consent for use of stored blood samples and research data for future research studies will also be collected, though any future research will obtain prior approval by a Human Research and Ethics Committee before commencement. The study will be conducted in accordance with the principles of the Declaration of Helsinki of 1975 (revised in 2013), according to international standards of Good Clinical Practice guidelines, applicable Australian government regulations, and Institutional research policies and procedures.

Outcomes of this RCT will be reported in international, high-quality, peer-reviewed journals, and the findings will be presented at national and international scientific conferences and meetings and through State and National representative bodies of exercise oncology and clinical hematology. Findings will also be communicated at community and consumer-led forums and will be presented at local hospital departments and university seminars.

## 7. Discussion

The aim of this study is to determine the impact of an individualized exercise program on patient-reported HRQoL, which has been shown to correlate with survival in people with MM at all disease stages [3,4,5,6,7]. Together with the effects on pain and fatigue, this will provide additional evidence of whether long-term improvements in HRQoL can be maintained whilst access to supervision is decreased. In addition, its effects on cardiorespiratory fitness, bone health, muscle strength, body composition, disease response, and select blood biomarkers will be analyzed. Assessment of changes in cardiorespiratory fitness, neuromuscular strength and power, and body composition, particularly bone and lean mass, will provide empirical evidence for the benefits of the program on the cardiovascular and musculoskeletal health of participants. Measures of bone turnover, adipokines, and immune functioning, as well as metabolomics, will enable investigation of changes in blood parameters that may affect disease survival. Semi-structured qualitative interviews and cost-effectiveness analyses will inform the potential for the program to be implemented as part of standard care for MM.

With the development of complex multi-novel-agent-based regimens for MM, a recent review highlighted the factors of importance to patients with MM in the real-world setting. These included symptom burden, treatment side effects and toxicities, and the ability to continue activities of daily living, including work productivity [111]. It suggested the need for collecting patient-reported outcomes to provide a more holistic definition of the effectiveness of treatment regimens. A strength of our proposed study is that it aligns with these objectives and, with the inclusion of patients at all disease stages, particularly during relapsed disease when symptoms and side effects of therapy may be most pronounced, provides a more comprehensive representation of MM in the clinical setting.

There are several limitations of the proposed study that warrant discussion. Our target population will be limited to those who are able to attend frequent testing and training visits and who are able to obtain an approval to participate from their treating physician. Arguably, those who are frailer, with limited mobility, and who may elicit a greater response from the intervention, will not be included in the study. Whilst the heterogeneous group of people with MM will demonstrate the ability of exercise to elicit improvements across the MM continuum, the study is not powered to conclude its effects within specific disease stages. Finally, the waitlist control group may increase their physical activity, despite being asked to maintain their activity levels for the first 12 weeks, reducing our ability to observe effects of the intervention.

## 8. Conclusions

The proposed study will provide novel evidence for the efficacy of exercise in improving quality of life, as well as providing a comprehensive battery of biophysical and psychosocial measures of health in people with MM. The safety, feasibility, acceptability, efficacy, and cost-effectiveness, as well as maintenance of effects of exercise, will be explored across a 12-month period. The potential findings of this proposed research will ultimately influence the inclusion of exercise as part of standard care to improve the health and longevity of people with MM.

## Figures and Tables

**Figure 1 curroncol-29-00077-f001:**
[figure not shown]
Schematic representation of the study protocol.

**Figure 2 curroncol-29-00077-f002:**
[figure not shown]
Schematic representation of the 12-week supervised exercise intervention protocol. HR_peak_: peak heart rate; OMNI-RES: OMNI-Resistance Exercise Scale of Perceived Exertion; reps: repetitions; mins: minutes.

**Table 1 curroncol-29-00077-t001:** Schedule of data collection.

	Timepoint			
Assessment or Outcome	Baseline ^a^	3-Months	6-Months	12-Months
*Screening*				
Participant eligibility	✓			
Informed consent	✓			
Doctor’s consent	✓			
Health history and disease status	✓	✓	✓	✓
Demographics	✓			
Concomitant research study participation	✓	✓	✓	✓
*Primary Outcomes*				
Quality of life (EORTC QLQ-C30 and QLQ-MY20)	✓	✓	✓	✓
*Secondary Outcomes*				
Cardiorespiratory fitness (V̇O2peak)	✓	✓	✓	✓
Body composition and bone mineral density (DXA)	✓	✓	✓	✓
Bone architecture (pQCT)	✓	✓	✓	✓
Anthropometry (BMI, waist, and hip circumferences)	✓	✓	✓	✓
Strength (30STS, grip strength, mid-thigh pull)	✓	✓	✓	✓
Balance (Single leg stance, YBT)	✓	✓	✓	✓
Pain and bone pain (BPI, FACT-BP)	✓	✓	✓	✓
Fatigue (FACIT-F)	✓	✓	✓	✓
Functional disability (OLBPDQ)	✓	✓	✓	✓
Myeloma-specific PROs (FACT-MM, MyPOS)	✓	✓	✓	✓
Falls self-efficacy (FES-I)	✓	✓	✓	✓
Blood collection for blood biomarkers, metabolomics, and lipidomics	✓	✓	✓	✓
Self-reported physical activity (Godin)	✓	✓	✓	✓
Sedentary behavior and physical activity (ActiGraph™ accelerometry)	✓	✓	✓	✓
Exercise enjoyment (PACES-8) ^b^		✓		
*Tertiary Outcomes*				
Qualitative analysis (Semi-structured interviews)			✓	
Adherence ^c^		✓	✓	
Safety (Adverse and serious adverse events) ^c^		✓	✓	

^a^ Baseline testing battery is repeated for waitlist control group after three months of usual care. ^b^ PACES-8 survey will be administered at 4-, 8-, and 12-weeks during the exercise intervention. ^c^ Adherence and safety will be monitored continuously throughout the supervised and unsupervised intervention. EORTC QLQ-C30: European Organisation for Research and Treatment of Cancer Quality of Life Questionnaire Core 30; EORTC QLQ-MY20: European Organisation for Research and Treatment of Cancer Quality of Life Questionnaire—Multiple Myeloma module; DXA: Dual energy X-ray absorptiometry; pQCT: Peripheral quantitative computed tomography; BMI: Body mass index; 30 STS: 30-s sit-to-stand test; YBT: Y-Balance Test; BPI: Brief Pain Inventory; FACT-BP: Functional Assessment of Cancer Therapy—Bone Pain; FACIT-F: Functional Assessment of Chronic Illness Therapy—Fatigue; OLBPDQ: Oswestry Low Back Pain Disability Questionnaire; PRO: Patient-reported outcomes; FACT-MM: Functional Assessment of Cancer Therapy—Multiple Myeloma; MyPOS: Myeloma Patient Outcome Scale; FES-I: Falls Efficacy Scale—International; PACES-8: Physical Activity Enjoyment Scale 8.

## Data Availability

This protocol paper does not describe any data. However, the datasets during and/or analyzed during the described study will be available from the corresponding author on reasonable request.
